##### Child’s health status (4 years)

Information on the child’s health over the past two years will be assessed using a 9-item questionnaire completed by the mother. For each question (e.g., Did your child suffer from a concussion or head injury/experience a loss of consciousness/experience a high fever with delirium or coma, etc.), mothers will be asked to answer “yes” or “no”, and if “yes”, report on the child’s age at the time of the event, and if possible further details describing the situation.

##### Internalizing and externalizing problems (2½ and 4 years)

Internalizing and externalizing behavior problems are assessed by maternal report using the Child Behavior Checklist (CBCL; [131]), which is the most frequently cited measure of child psychopathology and has psychometric properties suitable for research. The CBCL consists of 100 statements about the child's behavior (e.g., Acts too young for his/her age). Responses for each item are 0 = Not True, 1 = Somewhat or Sometimes True, to 2 = Very True or Often True. The Internalizing Problems scale combines the Emotionally Reactive, Anxious/Depressed, Somatic Complaints, and Withdrawn sub-scales. The Externalizing Problems scale combines the Attention Problems and Aggressive Behavior sub-scales. A Sleep Problems sub-scale can also be obtained. This questionnaire replaces the BITSEA, administered at 16 months.

#### Teacher questionnaire

##### Internalizing and Externalizing Problems (4 years)

In order to have a third-party assessment of the child’s typical behavior, the children’s preschool teacher or day-care provider will rate internalizing and externalizing behavior problems using the Caregiver-Teacher Report Form (C-TRF). This is the teacher version of the Child Behavior Checklist (CBCL) described above [131], and has identical items and scales.

#### Telephone interviews

##### Breast milk consumption (Recruitment, 12-month post-flood, 16 months and 2½ years)

We have collected data on maternal breastfeeding history since the infant’s birth to estimate the total quantity of breast milk intake. The recruitment questionnaire and 12-month post-flood questionnaires included items asking mothers if they had breastfed their babies, for how long, and if they were currently breastfeeding. We conducted a telephone interview at 16 months and again at 2½ years if breastfeeding went beyond 16 months. Mothers were asked how long they practiced exclusive, predominant and mixed breastfeeding, respectively. The phone interview took up to 10 minutes in mothers who had breastfed. These data will allow greater understanding of any interactions between maternal stress and breast milk intake, and influence on infant development.

##### Maternal psychiatric diagnosis (16 months)

Mothers completed the semi-structured Mini-International Neuropsychiatric Interview-Plus version 6 (MINI-Plus 2010; [132]) during a phone interview with a clinical psychologist to determine any current or lifetime psychopathology diagnoses. We obtained information about the timing of any identified psychiatric episodes in relation to the participant’s pregnancy and the event of the 2011 Queensland flood.

#### Face-to-face assessments: mother and child (16 month, 2½ years, and 4 years)

##### Maternal height, weight and body composition (16 months, 2½ and 4 years)

These measures will be used as covariates in analyses of child physical outcomes. Maternal height and weight were obtained during the 16-month and 2½-year assessments. In addition, percent body fat (using Tanita electronic scales) (www.tanita.com) was assessed at 2½. All measures will be repeated at 4 years.

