**Model 1:***MPF neuroendocrine systems*. We propose that objective and subjective PNMS will activate a cascade of events leading to an increase in maternal, placental, and fetal cortisol terminating in altered HPA axis function and a lower stress response in the child. We predict that more severe objective/subjective PNMS will decrease activity of the placental/activity of the placental 11β-HSD2, resulting in increased levels of cortisol in placenta and fetal blood (cord blood). Moreover, more severe objective/subjective PNMS will also be associated with increased placental Corticotropin-releasing hormone (CRH) production that will, in turn, over-stimulate the maternal HPA axis and thus exacerbate maternal cortisol production and the inhibition of placental 11β-HSD2, resulting in higher levels of cortisol in placenta and fetal blood (cord blood).

**Model 2:***MPF immune systems and metabolic outcome*. We propose that more severe objective/subjective PNMS will be associated with increased maternal catecholamine levels (physiological response to stress) resulting in an abnormally high level of oxidative stress and pro-inflammatory cytokines in the placenta that will increase inflammatory and oxidative status of maternal and fetal blood, which will cause an increase risk in obstetric complications (such as preterm birth, low birth weight, intrauterine growth restriction and preeclampsia), which may then go on to predict future risk for metabolic and psychiatric difficulties in children later in life.

**Model 3:***Birth weight and body composition*: We propose that higher placental cortisol levels will cause a decrease in the production of placental hormones regulated by glucocorticoids (such as human placental lactogen (hPL), placental growth hormone (pGH), leptin, estrogens, progesterone, and glucose transporter type 1(GLUT1; lower maternal-fetal glucose exchange)) resulting in a lower placental efficiency (lower birth weight and higher placental weight), resulting in fetal growth restriction and/or altered programming of body composition in the child. We hypothesize also that maternal and fetal glucose, insulin, leptin, and other adipocytokines in blood will be involved in this process.

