## Methods/design: QF2011

### Participants

All women who agreed to participate in the study provided written informed consent. Inclusion and exclusion criteria differed slightly for M@NGO [63, 64] and for QF2011. Women were eligible for recruitment to the M@NGO trial if they were less than 24 weeks pregnant and were not planning caesarean section birth; QF2011 participants had to have been pregnant with a singleton pregnancy (at any gestation) and residing in the general vicinity of Brisbane on January 10, 2011. All participants were 18 years of age or older at recruitment, and were able to speak English fluently.

Recruitment for QF2011 began as soon as ethics approval was received (April 4, 2011), and continued to mid-January 2012 (12 months after the peak of the flood); as per original protocol, recruitment for M@NGO ceased on May 31, 2011 in both Sydney and Brisbane. Recruitment proceeded in 4 ways:When new participants were recruited into M@NGO, they were also presented with the QF2011 protocol, and invited to participate in either or both studies. M@NGO recruitment at the Mater Hospital involved face-to-face, phone, and e-mail recruiting following a routine mail-out describing the study to all women attending the antenatal clinic.The team contacted all existing M@NGO subjects who were eligible for QF2011 first by e-mail, then by cell phone (text message), then by telephone inviting them to also participate in the new flood study.The team invited women who were pregnant and eligible for the QF2011 study, but not eligible for M@NGO, or who would have been eligible for M@NGO but were approached after M@NGO recruitment ceased, to participate in QF2011. A flyer inviting women to participate and to contact the recruitment team was included in the routine mail-out from the antenatal clinic. A researcher in the antenatal clinic actively recruited participants face-to-face on site and was available to speak to midwives and other potential participants about the study.Finally, advertisements were placed in local newspapers, on radio, and on the internet for women who were pregnant at the time of the floods (even if they had already delivered).

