**Maternal assessment: Face-to-face evaluation or phone Interview**										
Breast Milk Consumption Interview						Q				
Maternal Sensitivity (Emotional Availability Scales)						Q	Q			
MINI diagnostic interview (conducted once)						Q				
Mother height, weight, and % body fat (father if present)						Q	Q	Q		
Wechsler Adult Intelligence Scale (WAIS)										
National Adult Reading Test (NART)								Q		

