**Medical records**										
Labour/Delivery; Skin-to-skin time, Birth weight; Gestational age; APGAR; Length; Head circumference; Neurological @ Dch; Maternal height and weight; BMI; Weight gain			M							
Baby sex; Anomalies; Ultrasound report; Blood test reports; Glucose tolerance; Cord blood gas report, Doppler report of uterine and umbilical blood flow, Rx in pregnancy			Q							

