#### Routine database and chart audit

##### Mother’s chart

We requested the extraction of 273 variables from ‘Matrix’, the Mater Mother’s Hospital database. These variables include (but are not limited to): maternal height and pre-pregnancy weight (BMI); all medications prescribed during pregnancy; blood test reports from routine visits (first visit, 16-20 weeks (optional), and 26-28 weeks (incl. glucose tolerance)); and obstetric outcomes.

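### The only maternal size covariates named for child physical outcomes are measured after the flood and after birth; if flood stress affects later maternal weight or fat, adjusting for them can bias the total flood effect

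*Protocol article*

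**What the plan says.** The covariates are fixed in the protocol article's section on maternal height, weight and body composition (16 months, 2½ and 4 years): "These measures will be used as covariates in analyses of child physical outcomes". On timing, "Maternal height and weight were obtained during the 16-month and 2½-year assessments", while "percent body fat (using Tanita electronic scales) (www.tanita.com) was assessed at 2½" years; all are to be repeated at 4 years. Table 1 has a single row, "Mother height, weight, and % body fat (father if present", marked at all three visits. It therefore also implies body fat at 16 months, which the text does not mention.

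Exposure is dated by the inclusion criterion under Participants: women had to be pregnant and "residing in the general vicinity of Brisbane on January 10, 2011".

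A measure from before exposure was requested. The Mother's chart section lists "maternal height and pre-pregnancy weight (BMI") among the variables asked for from the hospital database. The medical-records part of Table 1 lists "Maternal height and weight; BMI; Weight gain" in the delivery column, without saying that the BMI is pre-pregnancy. Neither place gives these variables a role in an analysis.

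The outcomes concerned are central. Model 3 ends "resulting in fetal growth restriction and/or altered programming of body composition in the child", and obesity is named under research question 7 and among the ice-storm findings that the study aims to replicate and extend.

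**The concern.** The primary research question asks how much of the variance in outcomes is explained by the components of flood stress. That is a total-effect question, and no section narrows it to an effect net of the mother's later weight. Adjusting for a variable measured after exposure is safe for a total effect only if the exposure does not act on it. Maternal weight and fat 16 months to 4 years after birth follow pregnancy weight gain, postpartum weight retention and breastfeeding, any of which stress might alter.

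The article's own reasoning points the same way. It argues that disaster exposure is close to random and independent of family attributes, which reduces the need to control for confounders. If so, a link between flood stress and later maternal weight would arise largely through what happened after the flood, and conditioning on that weight controls little confounding. The regression strategy also enters exogenous variables before stress, and maternal weight years after the flood is not exogenous. At stake is an understated or distorted flood effect on child growth and adiposity.

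**Working it through.** The article gives no effect size, sample size or power figure for this point, so there is nothing to reproduce. The check has two parts.

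**1. Timing.** The earliest 16-month visit belongs to a child born just after the flood: 16 / 12 = 1.3 years after exposure. The latest 4-year visit belongs to a child conceived just before it: (9 + 48) / 12 = 4.75 years. Every named weight and fat value is therefore post-exposure. Pre-pregnancy weight precedes exposure for every eligible woman, because all were already pregnant on the flood date.

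**2. Size, under assumptions.** All three inputs are assumed, in SD per SD, because the documents give none:
- a, flood stress to later maternal weight or fat: 0 to 0.20
- b, later maternal weight or fat to child adiposity: 0.2 to 0.3
- c, total flood effect on the child: 0.15 to 0.25

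In a linear model c = c′ + a·b. Adjusting for the later measure returns c′, so the share removed is a·b / c.

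| a | b | c = 0.15 | c = 0.20 | c = 0.25 |
|---|---|---|---|---|
| 0 | either | 0% | 0% | 0% |
| 0.05 | 0.2 | 6.7% | 5.0% | 4.0% |
| 0.05 | 0.3 | 10.0% | 7.5% | 6.0% |
| 0.10 | 0.2 | 13.3% | 10.0% | 8.0% |
| 0.10 | 0.3 | 20.0% | 15.0% | 12.0% |
| 0.20 | 0.2 | 26.7% | 20.0% | 16.0% |
| 0.20 | 0.3 | 40.0% | 30.0% | 24.0% |

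The extremes are 0 and 0.20 × 0.3 / 0.15 = 40%.

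A simulation of 400,000 observations checked this with c = 0.20 and b = 0.3. Pre-pregnancy BMI was independent of flood stress, had a coefficient of 0.8 on later BMI, and acted on the child only through later BMI. An unmeasured common cause of later maternal weight and child adiposity had effect u on each. The table shows the estimated flood effect by adjustment set:

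| a | u | Pre-pregnancy BMI | Later BMI | Both |
|---|---|---|---|---|
| 0 | 0 | 0.201 | 0.201 | 0.201 |
| 0 | 0.3 | 0.199 | 0.198 | 0.198 |
| 0.10 | 0 | 0.202 | 0.172 | 0.171 |
| 0.10 | 0.3 | 0.199 | 0.159 | 0.143 |
| 0.20 | 0 | 0.199 | 0.140 | 0.139 |
| 0.20 | 0.3 | 0.200 | 0.122 | 0.084 |

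Adjusting for pre-pregnancy BMI recovers 0.20 throughout. Adding it beside later BMI repairs nothing and, with a common cause, makes matters worse.

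**Direction.** With later BMI alone in the model, the common cause shifts the estimate by −a·u₁·u₂ / (1 − a²), where u₁ and u₂ are its effects on maternal weight and on the child. For a = 0.20 and both effects 0.3, this is −0.20 × 0.09 / 0.96 = −0.019, and 0.14 − 0.019 = 0.121, which agrees with the simulated 0.122. If the two effects had opposite signs the shift would be +0.019, giving 0.159. The adjusted estimate would exceed the total effect only if |u₁·u₂| / (1 − a²) were larger than b. It would also exceed it if flood stress lowered later maternal weight: a = −0.10 and b = 0.3 give 0.20 + 0.03 = 0.23.

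**The case against.** A reader might infer that the later measures are used in place of pre-pregnancy BMI. The documents do not support that. Only the later measures are named as covariates, but nothing excludes pre-pregnancy BMI, the analysis section calls itself a sampling of approaches, and a condensed article may leave the full covariate list elsewhere. Nor is BMI shown to be in hand; its extraction was requested.

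A reader might also infer that part of the flood effect is certainly lost. That needs flood stress to change later maternal weight or fat, and that change to alter child size. No section states or quantifies either. Model 3 runs through placental cortisol, hormones and efficiency, not later maternal weight. If a = 0, nothing is removed.

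Two further points are fair. The article is about fetal programming, so adjusting for concurrent maternal size could be meant to isolate the prenatal route. And the article does not say in which block maternal weight enters; if it came after objective stress, the variance explained at the stress step would be untouched.

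These points limit the claim but do not remove it. The sentence on covariates is a stated choice, not missing detail. No section sets a direct effect as the target, and adjusting for later weight would not cleanly give one if common causes are unmeasured. Also including pre-pregnancy BMI would not help while later weight stays in the model.

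**Conclusion.** The point holds in conditional form. The only maternal size covariates that the article names for child physical outcomes are post-exposure. Maternal weight and percent body fat among them can bias the total flood effect on child growth and body composition if flood stress affects them. Adult height is not a concern.

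The size is unknown. Under the assumed linear paths it runs from no bias to a loss of 40% of the effect. Attenuation is the likelier direction if stress raises later weight, but it is not guaranteed. This is a worthwhile, inexpensive improvement to the plan, not a demonstrated error in a result.

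**What to change.** In the section on maternal height, weight and body composition, name maternal height and pre-pregnancy BMI from the hospital database as the maternal covariates in the main analyses of child physical outcomes. State that later maternal weight and percent body fat enter only a sensitivity or mediation analysis. At the same time, reconcile the text with Table 1 on whether maternal body fat was measured at 16 months.

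The cost is a sentence or two, and no new measurement where database records exist. The downside is coverage. The database belongs to one hospital, and some women were recruited through advertisements, in some cases after delivery. Whether it holds pre-pregnancy BMI for them is not stated, so the value may be missing or self-reported, and the plan should say how that is handled. The 4-year assessment began in 2015, so the change can still be useful for those analyses.

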##### Maternal general intelligence (4 years)

Maternal IQ will be estimated using the National Adult Reading Test (NART; [133]). The NART contains a list of 50 increasingly difficult words that are all irregular to the common rules of pronunciation. Individuals are asked to read the words aloud and the number of errors in pronunciation is recorded. Predicted Full-scale IQ and Verbal or Performance IQ is estimated by entering the number of errors into one of three formulas (e.g. Predicted Full-scale IQ: 130.6 – (1.24 X Errors). The NART has high inter-rater (0.97) and test-retest (0.98) reliabilities [134, 135]. It has also been demonstrated that the NART loads highly (0.85) on the same general intelligence factor that is obtained when factor analysis is performed on the sub-scales of the Wechsler Adult Intelligence Scale [136].

##### Child body composition measures (16 months, 2½ and 4 years)

Children’s height, weight and head circumference were measured, along with anthropometric measures, at 16 months and 2½ years, and will be repeated at 4 years. Anthropometric measures include mid-upper arm, waist and calf circumferences, as well as triceps and subscapular skinfolds. These measures allow calculation of body composition, which provide a better indication of metabolic risk than weight alone [137].

##### Cognitive and motor functioning (16 months and 2½ years)

The Bayley-III Scales of Infant and Toddler Development [138] were used to measure cognitive and motor development. The cognitive scale includes items that assess thinking and problem solving. The motor scale assesses fine and gross motor skills. The Bayley provides four types of norm-referenced scores: scaled scores, composite scores, percentile ranks and growth scores. It has been used extensively in research and is generally recognized as the ‘gold standard’ tool to assess development of very young children.

##### IQ (4 years)

The Wechsler Preschool Primary Intelligence Scale – Australian Standardized Version-III (WPPSI-III Australian; [139]) -- will be administered to assess the children’s intellectual functioning in general, verbal, performance, and cognitive domains. It is considered the gold-standard IQ test in early childhood. The Block Design and Information sub-scales will be administered as this dyad provides an excellent estimation of the Full Scale IQ (r = 0.92).

##### Visual-motor integration (2½ years)

The Beery-Buktenika Developmental Test of Visual Motor Integration – 6^th^ edition (VMI; [140]) was used to test children’s perceptual-motor ability. The child was presented with a booklet with a drawing on one page and a blank page opposite on which the child was to reproduce the image. The drawings are rated for accuracy and scored according to age norms.

##### Behavioral stress reactivity (16 months and 2½ years)

We included a brief stressor in the face-to-face assessments in order to evaluate the child’s stress reactivity, both biologically (see below) and behaviorally. At both ages, the mother left the child alone in the testing room for up to three minutes while the child was observed via one-way mirror. The separation was terminated prior to three minutes if the child demonstrated excessive crying, or at the mother’s request. All separation sessions were videotaped for later behavioral coding. The separation-reunion clip will be coded for infant stress reactivity using an in-house coding scheme currently in development.

##### Theory of Mind (2½ and 4 years)

TOM permits young children to understand their social world and predict and make sense of other people’s behavior. For a child to exhibit TOM, they must disengage thinking about themselves and understand that other people may have mental states that differ from their own [141]. We used two Diverse Desires tasks to assess TOM at 2½ years of age. In the first task, the child is presented with a choice of two snacks (apple and cookie) and asked which he/she prefers. The child is then told that Big Bird prefers the other snack. Then the child is asked which snack Big Bird would choose to eat, given the choice. The second task is identical, but involves two play activities (bike riding or a slide) and Snoopy. The child receives one point for each task for which they correctly identify the “other desire” rather than their “own desire” in answer to the question.

At 4 years, we plan to assess TOM using the Unexpected Contents Task [142] which, similar to the Diverse Desires tasks, tests the child’s ability to make a judgment about what other characters know and what they are likely to do. The child is shown what is inside a distinctive container (e.g., pencils in a Smarties box) and has to judge what another character, who did not see what was in the box, believes to be inside the container.

##### Attention and executive functioning (4 years)

Attention and Executive Functioning will be assessed using the Statue sub-scale of the Developmental NEuroPSYchological Assessment – second edition (NEPSY-II; [143]). For this task, the child is asked to remain still with their eyes closed for 75 seconds and inhibit impulses to respond to distracting sounds. The number of instances in which the child does not remain still is recorded.

##### Effortful control (4 years)

Effortful control describes the ability to exert self-control with the intention of obtaining greater delayed reward(s). An adaptation of the ‘marshmallow’ self-control task developed by Mischel, Ebbesen and Zeiss [144] will be used to assess children’s level of effortful control. Children will be instructed to sit in a room, alone at a table, with a desired snack in front of them. They will then be given the choice to either eat the desired snack, or wait ten minutes to receive two of their desired snacks. The time before the child eats their snack(s), and the child’s behavior throughout the task, will be recorded for later analysis.

